# Topiramate versus naltrexone for alcohol use disorder: study protocol for a genotype-stratified, double-blind randomised controlled trial (TOP study)

**DOI:** 10.1186/s13063-018-2824-z

**Published:** 2018-08-16

**Keywords:** Topiramate, Alcohol use disorder, Pharmacogenetics, Naltrexone, Alcohol dependence, GRIK1, OPRM1

## Abstract

**Background:**

Current treatments for alcohol use disorders have limited efficacy and there is a high degree of variability in treatment response. In a randomised, placebo-controlled clinical trial, there was a large effect size for topiramate in people homozygous for the *GRIK1* rs2832407*C allele. The primary aim of the TOP study is to examine prospectively the therapeutic and cost-effectiveness of topiramate versus an active control (naltrexone) in improving treatment outcomes for alcohol dependence. Participants will be stratified on rs2832407 to compare C-allele homozygotes with A-allele carriers to examine the moderating effect of rs2832407 on drinking outcomes. An exploratory aim is to examine the moderating effects of rs1799971, a polymorphism in *OPRM1*, on the response to naltrexone by comparing Asn40 homozygotes with Asp40 carriers.

**Methods/design:**

This double-blind trial will randomise 180 alcohol-dependent participants to a 12-week regime of either topiramate (titrating the dose up to 200 mg/day) or naltrexone (50 mg/day). Participants will be stratified on the two polymorphisms before randomisation. All participants will receive medical management. The primary drinking outcome will be the number of heavy drinking days per week and secondary drinking outcomes will include the time to relapse, the time to lapse and the percentage of abstinent days. Other secondary outcomes will include body mass index, tobacco use, anxiety symptoms and depressive symptoms.

**Discussion:**

If successful, the TOP study will improve management strategies for alcohol dependence by providing support for the use of genetic biomarkers to inform medication selection.

**Trial registration:**

ClinicalTrials.gov, NCT03479086. Registered on 27 March 2018.

**Electronic supplementary material:**

The online version of this article (10.1186/s13063-018-2824-z) contains supplementary material, which is available to authorized users.

## Background

Alcohol consumption is a leading cause of preventable death and is associated with over 200 diseases [1]. Although pharmacological treatment of alcohol use disorder (AUD) is now widely accepted, current treatments have modest efficacy and there is a high degree of variability in treatment response. Topiramate is increasingly being prescribed for AUD and its use now exceeds that of acamprosate, disulfiram and injectable naltrexone combined in the US veteran health system [2]. Topiramate antagonises glutamate activity at AMPA and kainate receptors [3], facilitates GABAergic function [4] and reduces the extracellular release of dopamine in the mesocorticolimbic region [5].

A recent meta-analysis of 1125 patients concluded that topiramate has a beneficial effect on heavy drinking and abstinence, with a somewhat larger effect size than naltrexone and acamprosate [6]. In alcohol-dependent patients, topiramate has also been observed to be efficacious in reducing body mass index (BMI) (by 1.2 kg/m^2^) relative to placebo [7], smoking rates [8] and symptom severity for anxiety and obsessive–compulsive disorder [9]. Effective interventions for psychological and physical conditions that are comorbid with AUD are particularly pertinent given their combined detrimental impact on the individual and the health-care system.

While a moderate signal of efficacy for topiramate in reducing heavy drinking has been demonstrated, there have been no well-controlled or well-powered direct comparative trials of topiramate with other commonly prescribed alcohol pharmacotherapies to guide treatment practice. Naltrexone was selected as the comparator for this trial because it is widely available as the standard of care for the pharmacotherapy of AUD [10]. One non-randomised, open-label trial showed that topiramate (200 mg/day) reduced alcohol intake and cravings significantly more than naltrexone [11]. The only randomised controlled trial (RCT) of topiramate versus naltrexone showed a non-significant trend towards a superior effect of topiramate, but the sample was small (*n* = 28) [12]. In addition, there have been very few economic evaluations of commonly prescribed medications for AUD [13, 14]. This absence of information on costs and potential economic benefits of treatment, given the significant burden of alcohol dependence, limits informed decision making by clinicians and policymakers.

The development of a personalised approach to treatment is an opportunity to improve the cost-effectiveness of pharmacotherapy by avoiding medications in patient groups unlikely to benefit or likely to experience adverse events. The heterogeneity in the effectiveness of alcohol pharmacotherapy may be related to variation in the genes encoding proteins involved in the specific mechanism of action of different drugs. Topiramate selectively acts on AMPA/kainate receptors via the GluK1 and GluK2 kainate subunits, which are encoded by genes *GRIK1* and *GRIK2*, respectively [4]. Variation in *GRIK1* has been demonstrated to be associated with alcohol dependence whereby the C allele of the single nucleotide polymorphism (SNP) rs2832407 was significantly overrepresented in individuals with alcohol dependence [15]. This provided the basis for studies of rs2832407 as a moderator of the response to topiramate. A secondary analysis of this hypothesis in a sample of 51 heavy drinkers showed that rs2832407*C-allele homozygotes reported fewer adverse events when treated with topiramate but no effect on treatment outcome [16].

More recently, a RCT demonstrated a robust moderating effect of rs2832407 on the therapeutic response to topiramate in a planned retrospective analysis [17]. This 12-week study demonstrated that patients treated with topiramate (with the dosage gradually increased from 25 mg/day to 200 mg/day) experienced fewer heavy drinking days (HDDs) per week than placebo-treated participants and higher odds of an abstinent day during week 12 in the topiramate group (odds ratio 2.57). This study demonstrated a large treatment effect in the rs2832407*C-allele homozygotes but not in the A-allele carrier group. In CC individuals treated with topiramate, the number needed to treat based on the criterion of no HDDs in the last 4 weeks of treatment was 2.28 compared to the full sample number needed to treat of 5.29. Similarly, the number needed to harm based on the presence of any severe adverse event was 9.09 compared to the full sample number needed to harm of 7.35. Thus, not only did CC individuals benefit from topiramate treatment, they also tolerated it better than A-allele carriers. In a follow-up analysis, these authors observed a moderating effect of positive alcohol expectancies on the relationship between rs2832407 and topiramate during treatment [18]. The beneficial effect of topiramate on daily drinking in CC individuals was lessened on days when these participants reported higher levels of anticipated positive outcomes of drinking. It is important to note that, although the results from this trial are promising for personalised medicine, they are based on secondary analyses rather than participants being prospectively stratified on genotype. This does not guarantee equivalence of group size nor baseline characteristics that may moderate or mediate treatment outcome.

The majority of naltrexone pharmacogenetic studies have examined the role of rs1799971 (or Asn40Asp), a SNP in the gene encoding the mu-opioid receptor (*OPRM1*), as a moderator of treatment response. Most retrospective analyses have shown greater treatment efficacy in heavy drinkers with Asp40 who were treated with naltrexone [19, 20]. However, more recently, data from two prospective studies that oversampled the variant allele failed to show a moderating effect [21, 22]. These inconsistencies are most likely due to the sampling bias inherent in post hoc analyses of clinical trial data [21]. Prospective genotype-stratified trials are required to confirm retrospective observations from a secondary analysis of pharmacotherapy trials.

Accordingly, the current study aims to examine the treatment and cost-effectiveness of topiramate versus naltrexone in improving outcomes in active drinkers and prospectively to examine the moderating role of the rs2832407 polymorphism in *GRIK1* on treatment response. We hypothesise that:i.Topiramate-treated patients will significantly reduce their drinking, as measured by the number of HDDs, compared to oral naltrexone.ii.Topiramate treatment will be more cost-effective than oral naltrexone.iii.rs2832407 will have a moderating effect on drinking outcomes in topiramate-treated patients.iv.Comorbid clinical conditions (e.g. obesity, smoking rates and anxiety) will be significantly improved in topiramate-treated patients compared to those on naltrexone.

We will also conduct exploratory analyses of the moderating role of (i) the Asn40Asp SNP in *OPRM1* on drinking outcomes in naltrexone-treated patients and (ii) baseline clinical characteristics on treatment response to topiramate versus naltrexone. This article presents the protocol for the RCT and is written to comply with the recommended SPIRIT guidelines for RCT protocols (Additional file 1) [23].

## Methods/design

### Study objectives

We are conducting a 12-week, double-blind, randomised trial to examine the effectiveness of topiramate versus naltrexone in improving treatment outcomes for heavy drinkers.

### Patient recruitment

The trial is being conducted in several outpatient hospital settings across Sydney, NSW, Australia. We aim to recruit 180 participants by clinical referral from treating physicians, nurses and psychologists among inpatients and outpatients of participating hospitals. We will also recruit via flyers and community advertisements at local general practitioners, newspapers and websites. Based on our previous experience, recruitment from mixed sources does not significantly impact treatment retention or outcome in alcohol pharmacotherapy trials [24]. After detoxification according to local procedures as clinically indicated, consenting participants enter the study. Participant time and travel expenses are reimbursed at the follow-up research assessments.

### Randomisation and allocation concealment

The study is a double-blind, randomised trial with participants being randomised to receive one of two possible medication arms. The study is conducted under double-blind conditions so that participants and study staff are unaware of medication assignment. A computer-generated random allocation to topiramate or naltrexone is being provided by an independent service at the Clinical Trials Centre of the National Health and Medical Research Council (NHMRC) in Australia using minimisation stratified by *GRIK1* genotype, *OPRM1* genotype and the concurrent use of antidepressants. This is provided to the clinical trials pharmacist at each site for allocation to an intervention and dispensing medication. Researchers, clinicians and participants are all blinded to treatment allocation. In the event of a medical emergency that requires knowledge of the treatment condition in the opinion of the treating clinician at the time, the investigators can contact the 24-h telephone service at the NHMRC Clinical Trials Centre to break the randomisation code for that individual.

### Inclusion and exclusion criteria

#### Inclusion criteria

The inclusion criteria are:Aged 18 to 70 yearsAUD according to the DSM-5 criteriaAdequate cognition and English language skills to give valid consent and to complete research interviewsAverage weekly alcohol consumption of ≥30 standard drinks for men and ≥25 standard drinks for women, with a weekly average of ≥2 HDDs during the month before screeningWritten informed consentWillingness to provide a blood sample for genotyping

#### Exclusion criteria

The exclusion criteria are:Active major psychiatric disorder associated with psychosis, significant suicide risk, or signs of impaired cognitive functioningPregnancy or lactation; women are advised to use reliable contraception for the duration of drug therapy and a urine pregnancy test is performed as appropriateConcurrent use of any psychotropic medication other than antidepressants (provided that these are taken at stable doses for at least 2 months)Currently taking any tricyclic antidepressant, e.g. Adapin (doxepin), Anafranil (clomipramine), Elavil (amitryptyline), Pamelor (nortryptyline), Tofranil (imipramine) or Sinequan (doxepin)Use of antiretroviral dolutegravirDependence on any substance other than nicotineOpioid abuse, opioid dependence or opioid agonist treatment, or likely need for opioid treatmentClinically decompensated liver disease (jaundice or other signs of liver failure)History of nephrolithiasisHistory of glaucomaLack of stable housing or contact phone numberPrevious hypersensitivity to topiramate or naltrexoneAny alcohol pharmacotherapy within the past month

### Procedures and schedule of visits

Patients are initially assessed for suitability by a medical officer and offered withdrawal management as clinically indicated. Suitable patients are offered screening. The schedule of enrolment, interventions and assessments is depicted in Fig. 1.

**Fig. 1 Fig1:**
[figure not shown]
SPIRIT figure of the TOP study protocol.

#### Visit 1 (screening visit)

At the screening visit (visit 1), patients are asked to provide informed consent by the research nurse. The research nurse obtains a structured medical and psychiatric history. Blood and urine samples are taken for clinical laboratory evaluations (see below).

#### Visit 2a (baseline visit)

Eligible patients undergo a research evaluation (90–120 min) 2–7 days after screening, during which time genotyping and if necessary alcohol withdrawal management are completed. A study physician performs a physical examination.

#### Visits 2b to 10 (treatment and follow-up visits)

Patients receive initial counselling and study medication during a treatment session (2b) on the same day as the baseline visit (2a). Patients are given either naltrexone 50 mg/day or topiramate titrated up to a maximum of 200 mg/day by week 6 (see below for details). During the 12-week treatment period, patients return weekly for medical management and medication dispensing for the first 6 weeks and then every 3 weeks until the end of the treatment period. They return for the final follow-up medical review and research appointments at weeks 12 and 24.

### Pharmacotherapy schedule

#### Topiramate

The maximal dosage of topiramate is 200 mg/day in two divided doses based on prior evidence of efficacy, tolerability and high completion rates [12, 25]. Topiramate is registered as a prescription medication in Australia (Australian Register of Therapeutic Goods IDs 135797, 135790 and 135,766) and is purchased from Sandoz Pty Ltd. A gradual 6-week titration period that was well tolerated in previous studies is used [17]. The dose of topiramate is not increased if the previous dose is not well tolerated (in previous experience, for <5% patients), as indicated by the reporting of adverse events, the discretion of the physician or at the request of the participant. The nurse will provide guidance for patients on the titration schedule in consultation with the study physician. The schedule isWeek 1: 25 mg afternoonWeek 2: 50 mg afternoonWeek 3: 75 mg (25 mg morning and 50 mg afternoon)Week 4: 100 mg (50 mg morning and 50 mg afternoon)Week 5: 150 mg (50 mg morning and 100 mg afternoon)Weeks 6–12: 200 mg (100 mg morning and 100 mg afternoon)

#### Naltrexone

The dosage of naltrexone is 50 mg daily. This group receives two capsules per day to match the topiramate dosage (placebo in the morning and naltrexone in the afternoon). Naltrexone is registered as a prescription medication in Australia (Australian Register of Therapeutic Goods ID 128710) and is purchased from Generic Health Pty Ltd.

Medications are over-encapsulated to maintain the double-blind and formulated in two different coloured capsules (morning versus afternoon doses). At the end of the 12-week treatment period, the participant and the researcher are asked to record the drug the participant is thought to have received. Limiting the dose (rather than titrating upwards) is permitted according to clinician judgement and is recorded to optimise treatment outcome by minimising side effects and maximising adherence. Participants who wish to cease medication are advised to withdraw medication gradually over 1 week. Any participants who wish ongoing treatment are offered open-label pharmacotherapy at their own expense subject to the judgement of their clinicians. Clinical data for any such individuals are being collected.

### Medical management

At each treatment visit, all patients receive 20–30 min of medical management, which was developed for the COMBINE trial as a medically oriented intervention to maximise medication adherence in the treatment of AUD [26]. Clinicians with minimal specialty training who are knowledgeable about AUD can deliver this brief, effective and widely used intervention. Medical management is, thus, feasible in all study sites and unlikely to obscure a medication effect on drinking outcomes. In medical management, the clinician highlights the participant’s symptoms related to problematic alcohol use and the need for treatment. The participant is advised to reduce or stop drinking, educated about alcohol-related disorders, given a rationale to take medication, instructed on the importance of medication adherence and given information on the medications. The research nurse also checks the participant’s breath alcohol level, vital signs and weight, medication adherence, drinking and smoking, and general functioning, and obtains a urine sample to measure medication adherence. Participants provide reports of side effects at each study visit. Patients are asked to return unused study medication at each treatment visit. Capsule counts and usage are recorded. Participants will be encouraged to defer concurrent psychotherapy until at least week 6 of the trial.

### Study assessments

#### Medical and laboratory tests

Medical and laboratory tests are to screen participants for exclusion criteria, assess potential adverse effects, provide objective measures of alcohol use, and assess covariates and secondary outcome measures. The physical examination at baseline includes a blood pressure and cardiovascular examination, checks for alcohol-related liver disease, a brief neurological examination and a mental state examination. Blood and urine are obtained at screening and at weeks 6, 12 and 24. Laboratory tests include: urinalysis, urine toxicology, full blood count, liver function tests (for bilirubin, gamma glutamyl transpeptidase, alkaline phosphatase, aspartate transaminase, alanine aminotransferase, albumin and protein), coagulation tests (international normalized ratio and activated partial thromboplastin time), creatinine and phosphatidylethanol. Bicarbonate and electrolytes are checked to screen for metabolic acidosis, an adverse effect of topiramate treatment that is readily reversible (weekly as required). Blood samples are also collected and stored for biochemical, genetic and molecular analysis in the current trial and for future use in ancillary studies.

### Psychological assessments

At baseline, demographics, medical history, personal and family history of AUD, and alcohol treatment history are obtained as in our previous trials [27–30]. Psychiatric diagnostic information is obtained with the MINI Neuropsychiatric interview [31]. The following measures are implemented at baseline and follow-up.Characteristics of alcohol dependence (baseline and follow-up):(i)Recent (last 30 days) alcohol consumption (frequency and quantity) assessed by the timeline follow-back method (TLFB) [32], with which we also measure tobacco use(ii)Severity of alcohol dependence assessed by the Alcohol Dependence Scale [33](iii)Craving for alcohol measured by the Penn Alcohol Craving Scale [34](iv)Drinker Inventory of Consequences (at baseline and at follow-ups) [35], which provides a measure of the social, physical and emotional consequences of alcohol use(v)Tension Reduction Alcohol Outcome Expectancies, which measures expectancies regarding the outcome of alcohol use [36].Mental health:(i)Depression, Anxiety and Stress Scale, which measures the severity of symptoms of depression, anxiety and stress [37](ii)Sleep problems assessed by the Insomnia Severity Index [38]Motivation and self-efficacy:(i)Stages of Change Readiness and Treatment Eagerness Scale (SOCRATES) assesses motivation to change [39](ii)Alcohol Abstinence Self-Efficacy (AASE) scale measures perceived self-efficacy [40]Cognitive and executive function:(i)The Montreal Cognitive Assessment (MoCA), which is used to screen for cognitive impairment that is likely to preclude the completion of study procedures and treatment [41](ii)Trail Making Test [42], which is used to screen for impairment and to measure the speed of processing and executive functioningPhysical health:(i)Health outcomes measured using the EQ-5D questionnaire [43] and Health and Performance Questionnaire (HPQ) [44]

We also collect daily drinking, medication usage and alcohol expectancies via SMS (automated email to SMS). Daily paper diaries supplement SMS where necessary. An assertive follow-up will be made to obtain data for all randomised participants, regardless of whether they drop out of the study.

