### Primary outcome

The primary outcome is alcohol consumption expressed as self-reported number of HDDs (defined as at least four drinks for women and at least five drinks for men) per week. Any conflicting information will be validated by collateral reports and measurements of biological markers of alcohol consumption (phosphatidylethanol).

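### The follow-up TLFB looks back 30 days, so a participant silent on every channel until the week-12 interview leaves an avoidable gap in weekly heavy drinking days

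*Protocol article*

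**What the plan says.** All references are to the protocol article.

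- **Outcome.** Primary outcome gives "alcohol consumption expressed as self-reported number of HDDs" per week. Neither that section nor Statistical analysis names the instrument that supplies the weekly count.
- **Period.** Study objectives: "We are conducting a 12-week, double-blind, randomised trial". Statistical analysis compares weekly HDDs by mixed models, with a further contrast on the last six weeks of treatment.
- **Recall interview.** Psychological assessments lists "Recent (last 30 days) alcohol consumption (frequency and quantity) assessed by the timeline follow-back method (TLFB"), introduced by "The following measures are implemented at baseline and follow-up". One window therefore serves both occasions.
- **Research appointments.** Visits 2b to 10: "They return for the final follow-up medical review and research appointments at weeks 12 and 24".
- **Treatment visits.** The same section: "patients return weekly for medical management and medication dispensing for the first 6 weeks and then every 3 weeks until the end" of treatment. Under Medical management the nurse checks "vital signs and weight, medication adherence, drinking and smoking, and general functioning" at these visits.
- **Daily reports.** Psychological assessments adds daily drinking reports by SMS, with paper diaries as a supplement.
- **Dropouts.** Psychological assessments: "An assertive follow-up will be made to obtain data for all randomised participants, regardless of whether they drop out of the study". Statistical analysis also says that follow-up does not depend on staying on treatment.
- **Missing data.** Statistical analysis relies on ignorable missingness for the mixed model and adds multiple imputation and sensitivity analyses.

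**The concern.** The article undertakes to obtain data on everyone randomised, but the only retrospective day-by-day drinking instrument that it describes has a stated window much shorter than the treatment period. The other sources need continuing cooperation: nurse checks need an attended visit, and SMS or diaries need daily reporting. A participant who has stopped all of these, and is then traced and interviewed at week 12, is asked about 30 days and not about the silent weeks before them.

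What is at stake is mainly bias. Silence may well be related to drinking. It may also differ by arm: topiramate is titrated over six weeks and naltrexone is not. The Background reports, for topiramate in a placebo-controlled trial, a number needed to harm for severe adverse events of 7.35 overall and 9.09 in CC participants, so silence could differ by genotype too. That is a reason for care and not evidence about naltrexone as comparator. The gap also touches time to lapse and time to relapse, because a first drink inside it cannot be dated.

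**Working it through.** **Inputs.** Window 30 days (Psychological assessments). Treatment 12 × 7 = 84 days (Study objectives). Visits weekly to week 6, then every 3 weeks, so days 7, 14, 21, 28, 35, 42, 63 and 84. Power inputs from Sample size calculations: 90 per group, d = 0.33 from week 7 through week 12, within-subject correlation ρ = 0.35–0.40, two-sided α = 0.05. Assumption: the week-12 interview takes place on day 84.

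**1. The plan's own power figure.** For the mean of m weekly values under compound symmetry, v = (1 + (m − 1)ρ)/m and power = Φ(d·√(n/(2v)) − 1.96). With m = 6 (weeks 7–12):

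- ρ = 0.35: v = 2.75/6 = 0.4583; 0.33 × √(90/0.9167) = 3.270; power Φ(1.310) = 0.905.
- ρ = 0.40: v = 3.00/6 = 0.5000; 0.33 × √(90/1.0) = 3.131; power Φ(1.171) = 0.879.

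The stated power of more than 80% is reproduced. A single time point (v = 1) would give 0.600, so the claim rests on the repeated weeks.

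**2. What a 30-day window reaches at day 84.** First day reached: 84 − 30 + 1 = 55. Days 1–54 are not reached: 54/84 = 64%. These are weeks 1–7 in full and 5 of the 7 days of week 8. In the last six weeks (days 43–84), days 43–54 are not reached: 12/42 = 29%. At week 24 (day 168) the window reaches days 139–168, so it cannot fill the gap.

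**3. Who has a gap.** For attenders, the longest interval between visits is 21 days, inside 30. For a participant with no drinking data between the last report and week 12, the gap is max(0, 54 − last day reported):

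| Last day reported | Days missing | Share of 84 |
|---|---|---|
| 0 | 54 | 64% |
| 7 | 47 | 56% |
| 14 | 40 | 48% |
| 21 | 33 | 39% |
| 28 | 26 | 31% |
| 35 | 19 | 23% |
| 42 | 12 | 14% |
| 63 | 0 | 0% |

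**4. Effect on power.** The article gives no dropout rate, so let an assumed fraction f of participants have only weeks 9–12 of weeks 7–12. Then v₆ is as in step 1, v₄ = (1 + 3ρ)/4 = 0.5125 or 0.5500, information = 90·[(1 − f)/v₆ + f/v₄], and power = Φ(d·√(information/2) − 1.96).

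| f | ρ = 0.35 | ρ = 0.40 |
|---|---|---|
| 0 | 0.9049 | 0.8791 |
| 0.1 | 0.9019 | 0.8762 |
| 0.4 | 0.8925 | 0.8672 |
| 1.0 | 0.8712 | 0.8473 |

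Power stays above 80% throughout. These figures assume that missingness is unrelated to drinking, which is the assumption in doubt.

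**The case against.** The strongest reply is that the TLFB is one source among several. The article does not say that it supplies the primary outcome, and SMS and diaries do not depend on attendance. A reader might infer from the 30-day window that days 1–54 are lost for everyone, or for every dropout. The documents do not support that: someone who stops treatment but keeps texting supplies every week, and someone who attends visits is never more than 21 days from the last one.

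A reader might also conclude that the gap is missing by design. That goes too far. Nothing says that assertive follow-up waits until week 12, and contact within 30 days of the last report would leave no gap even under the literal window. The assessment schedule is in Fig. 1, which is not available here, and it may show the TLFB at other visits. That would not help people who have stopped attending.

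The plan also does not rest on ignorable missingness alone, since multiple imputation and sensitivity analyses are promised. Finally, a 30-day window beside daily SMS is a defensible choice, because longer recall is less precise.

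All of this stands and narrows the point. It does not help the participant who is silent on every channel and is next reached at week 12. For that person the window as written leaves out days that could be asked about, and imputation explores the loss without replacing the answer.

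**Conclusion.** The concern holds in a limited form. If the 30-day limit is applied as written, a participant with no visit, SMS or diary data until the week-12 interview has an unrecovered gap from the last report to day 54: 33 of 84 days after last contact at day 21, and at most 54 days for an interview on day 84. Anyone last heard from by day 42 loses 12 of the 42 days in the final-six-weeks contrast.

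The number of such participants cannot be computed, because no dropout or SMS-compliance rate is given. The effect on power is small. The remaining issue is bias of unknown size if silence is related to drinking, arm or genotype. This is a cheap improvement to a stated instrument window; it is neither a contradiction nor a flaw that threatens the trial.

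**What to change.** At every post-baseline TLFB, replace the fixed 30 days by a look-back to the last day with recorded drinking data, reaching back to randomisation at most for the week-12 interview. Let SMS and diary entries take precedence where they exist. State that the recovered days count towards the weekly HDD outcome, and so which sources define it. Keep the 30-day window at baseline.

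The cost is a change to the interview instruction and extra interview minutes for participants with gaps; those who attend or keep reporting are almost unaffected. Recall will be less precise than daily reporting, but only for days that would otherwise be missing. Trial status reports that recruitment was under way at publication, so the change would apply to participants not yet interviewed.
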